## Abstract

**Introduction:**

Approximately one in three of all older adults fall each year, with wide ranging physical, psychosocial and healthcare-related consequences. Exercise-based interventions are the cornerstone for falls prevention programmes, yet these are not consistently provided, do not routinely address all components of the balance system and are often not well attended. The HOLOBalance system provides an evidence-based balance training programme delivered to patients in their home environment using a novel technological approach including an augmented reality virtual physiotherapist, exergames and a remote monitoring system. The aims of this proof-of-concept study are to (1) determine the safety, acceptability and feasibility of providing HOLOBalance to community dwelling older adults at risk for falls and (2) provide data to support sample size estimates for a future trial.

**Methods:**

A single (assessor) blinded pilot randomised controlled proof of concept study. 120 participants will be randomised to receive an 8-week home exercise programme consisting of either: (1) HOLOBalance or (2) The OTAGO Home Exercise Programme. Participants will be required to complete their exercise programme independently under the supervision of a physiotherapist. Participants will have weekly telephone contact with their physiotherapist, and will receive home visits at weeks 0, 3 and 6. Outcome measures of safety, acceptability and feasibility, clinical measures of balance function, disability, balance confidence and cognitive function will be assessed before and immediately after the 8 week intervention. Acceptability and feasibility will be explored using descriptive statistics, and trends for effectiveness will be explored using general linear model analysis of variance.

**Ethics and dissemination:**

This study has received institutional ethical approvals in Germany (reference: 265/19), Greece (reference: 9769/24-6-2019) and the UK (reference: 19/LO/1908). Findings from this study will be submitted for peer-reviewed publications.

**Trial registration number:**

NCT04053829.

**Protocol version:**

V.2, 20 January 2020

Strengths and limitations of this studyThis study uses a pilot randomised control design to explore the safety, acceptability and feasibility of providing the HOLOBalance intervention compared with an established home exercise programme.The HOLOBalance programme provides an individualised training programme prescribed by a treating clinician which addresses all facets of the postural control system.The HOLOBalance study will use quantitative and qualitative data to explore the acceptability of providing holographic balance training programmes to older adults at risk for falls.This study will provide crucial insight into the feasibility of implementing state-of-the-art technologies in the home environment.This pilot study is not powered to determine whether HOLOBalance reduces falls risk or falls rate.

## Introduction

One-in-three people over the age of 65 fall annually.^1^ It is widely accepted that falls are multi-factorial in nature^2 3^ and that impaired balance function is associated with falls.^4^ Maintaining balance is complex and depends on sensory inputs from the visual, proprioceptive and vestibular systems to provide information on body position and motion. Alongside this, central processes monitor and control the interaction between musculoskeletal and neural systems to generate anticipatory postural adjustments and adapt posture to changing environmental and balance task demands.^5^ Age-related declines in these systems are well documented and lead to impaired postural and gait control thus increasing risk for falls.^6 7^ Recent studies have identified that vestibular dysfunction is common in older adults who fall,^6 8–13^ with up to 80% of fallers experiencing vestibular dysfunction.^9^ Although sensory inputs are crucial for postural control, cognitive functions are equally as important for maintaining safe community ambulation. Deficits in executive function and attention are common in older age and are associated with impairments in postural control, dual-tasking balance ability (ie, walk and talk at the same time), reduced gait speed and increased falls risk.^14–20^ Additionally, changes in cognitive function strongly predict impairment in activities of daily living and functional independence.^19 21–23^ Thus, falls must be considered as multifactorial in nature and should be targeted in interventions that address domains that impact on balance and quality of life.

As falls have wide-ranging physical and psychological consequences and increase the likelihood of frailty, cognitive decline, sedentary behaviour, social exclusion, injury and death,^5–7 21 24–26^ their prevention is of primary concern to many public health bodies.^27–29^ The National Institute for Health and Care Excellence UK guidelines^30^ recommend that older adults at risk for falls should undergo a balance assessment and receive targeted interventions to improve balance and reduce risk for falls. Despite the strength of available evidence, compliance and implementation for providing balance rehabilitation has been poor in UK healthcare settings.^31^

Balance rehabilitation typically consists of personalised sets of exercises, defined by a healthcare professional and is the only effective treatment for balance disorders, irrespective of a person’s age.^32–34^ Although exercises are typically brief and easy to perform, there is up to 50% lost to follow-up rate in older adults in these programmes, and while supervision significantly increases compliance and effectiveness,^35^ it is costly to provide. To this end, many falls prevention programmes provide exercise programmes completed either in group settings or independently at home.^36–41^ These programmes have been shown to be effective in reducing falls rates in older adults, reducing falls by 30%–40% (dependant on target population), however, they are limited in that they either do not provide exercises to address vestibular function or dual task training,^37–39^ or these are not introduced until very late in the programme.^40 41^ This is despite promising evidence suggesting that combined cognitive and functional training may provide improvements beyond single task training.^42–44^ Similarly, rehabilitation programmes which address vestibular dysfunction (ie, multisensory rehabilitation, MSR programmes) have been developed for older adults at risk for falls and have shown substantial additional reduction of falls risk to standard programmes.^45–47^ These programmes require customised, expert-led interventions to optimise recovery, however, there is limited availability of experts to provide these individualised interventions and these may hinder their translation into clinical practice.

The HOLOBalance telerehabilitation platform has been developed to address this lack of expert physiotherapists. HOLOBalance will provide a customised and interactive falls rehabilitation programme that incorporates: (1) functional balance training, (2) multisensory exercises to improve balance function and (3) cognitive-motor training, for older adults at risk for falls. HOLOBalance will use off-the-shelf technologies to allow clinicians to provide an individualised balance rehabilitation programme for older adults who will be able to participate in at a time of their choice and in their home environment (for system description please visit www.holobalance.eu). This study protocol outlines the multisite randomised controlled proof-of-concept study to explore safety, feasibility and acceptability of the HOLOBalance telerehabilitation system.

## Methods and analysis

### Trial design

This study is an assessor-blinded, randomised proof-of-concept study to explore the acceptability and feasibility of providing a home-based balance telerehabilitation programme (HOLOBalance) to community-dwelling older adults at risk for falls. All participants will be enrolled in a 8-week home exercise programme (HEP) designed to improve balance function, and which adheres to the current guidance for strength and balance training.^30^ All participants will receive an exercise programme provided under the supervision of a physiotherapist with regular reviews by telephone (weekly) and home visits (week 0, 3 and 6). Exercises will be prescribed according to participant feedback and task performance as assessed by the treating physiotherapist.

This study will compare acceptability of the HOLOBalance telehealth programme (eg, compliance, drop-out rate) to an established HEP that is routinely used in community rehabilitation (the OTAGO HEP^23^) and will explore trends for effectiveness across a number of validated outcome measures to explore whether a future trial is warranted, and if so to provide data for a sample size estimate. For this proof-of-concept study, data will be collected at baseline (week 0) and at completion of the intervention (week 9). The flow of participants through the trial will be recorded in compliance with the Consolidated Standards of Reporting Trials statement (figure 1), and this protocol has been developed using the Standard Protocol Items: Recommendations for Interventional Trials reporting guidelines for clinical trials.^48^

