### Inclusion criteria

Independent community-dwelling participants able to walk 500 m independently or with a stick.No significant visual impairment.Able to understand and to consent to the research.A score of >22 on the Montreal Cognitive Assessment (MoCA), that is, adults with no or mild cognitive impairment.At risk of falls (ie, Functional Gait Assessment, FGA less than 22/30), and / or have significant fear of falling (Falls Efficacy Scale International (FESI) short form >10) and /or have experienced a fall/s in the last 12 months.Willing to participate and to comply with the proposed training and testing regimen.Available space of 1×2 m at home and sufficient home broadband to allow the system to operate as designed.

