### Randomisation

Patients will be randomised using an online platform (www.sealedenvelope.com) into either the intervention or control groups. Participants will be allocated in blocks of 10 with an allocation ratio of 1:1 to control (OTAGO HEP) and intervention (HOLOBalance) groups. Randomisation procedures will be run independently for each site and will be completed by a researcher external to the research study. No out of hours randomisation is required for this study.

Allocation will be concealed in consecutively numbered opaque envelopes which will be drawn up for each block and presented to the treating physiotherapist after the baseline assessment session has been completed. Allocation will not be revealed until after the baseline assessment has been completed, and once revealed will be entered onto the enrolment log.

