### Data management and statistical analysis

Anonymised data will be entered into a study database. The integrity of this data will be assessed by taking a random sample (10%) from the study database (after the completion of data collection) and comparing with the paper case report form (CRF). If there is less than 98% agreement between the paper CRF record and inputted measures, all data will be checked and rectified. The rectified database will be saved under a new filename (eg, studydatabase_rectified_date) and all changes made to the database will be logged. Essential trial documentation will be kept with the Trial Master File and Investigator Site Files. The sponsor will ensure that study documentation is retained in accordance with their local approvals after the conclusion of the trial.

As this is a proof-of-concept study, there is no formal plan for statistical analysis due to the small sample size and lack of statistical power. However, for a future trial an analysis plan has been developed which will be run in this study to determine its appropriateness. We will use intention to treat analysis with repeated measures general linear model analysis of variance for selected outcome measures and other appropriate tests for between-group and within-group analysis. We will also include correlations analysis and χ^2^ assumption testing.

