### Sample size

This proof-of-concept study will recruit 60 participants per group (ie, total sample size of 120). This will allow the researchers to gain preliminary data on the primary outcomes of safety, feasibility and acceptability of the HOLOBalance intervention. This will also provide sufficient data to explore trends for effectiveness and to allow for sample size estimates to be drawn up for a future trial.

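### Whether a future trial is warranted is tied to effectiveness trends over many scales that the study says it lacks power to analyse, which invites error in both directions

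*Protocol article*

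**What the plan says.** The Trial design section of the protocol article says the study "will explore trends for effectiveness across a number of validated outcome measures to explore whether a future trial is warranted". The same sentence adds a second use of the results, for planning: "and if so to provide data for a sample size estimate". The Sample size section states: "This proof-of-concept study will recruit 60 participants per group (ie, total sample size of 120". It asserts that this gives "sufficient data to explore trends for effectiveness and to allow for sample size estimates to be drawn up for a future trial", without an effect size, SD or precision target. Allocation uses an "allocation ratio of 1:1 to control (OTAGO HEP) and intervention (HOLOBalance) groups".

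The section on data management and statistical analysis says "there is no formal plan for statistical analysis due to the small sample size and lack of statistical power". It also says that a plan developed for a future trial will be run here: repeated measures analysis of variance on selected outcomes, with "other appropriate tests for between-group and within-group analysis".

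Table 2 lists 11 instruments at both baseline and follow-up: MoCA, RAPA, WHODAS 2.0, CANTAB, ABC, FES-I, EQ-5D, EMA, BREQ-3, mini-BESTest and FGA. The primary outcomes are acceptability, safety and feasibility. Under Inclusion criteria, one route to entry is "At risk of falls (ie, Functional Gait Assessment, FGA less than 22/30"); a short FES-I score above 10 or a fall in the past 12 months also qualifies.

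**The concern.** The article denies that the study has the power for a formal analysis of effectiveness, then links the case for a further trial to what that analysis shows. A trend is not defined. Looking over many scales raises the chance that a null intervention appears promising somewhere. Low power on each scale raises the chance that a useful one appears unpromising.

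Within-group tests add a separate problem. Both arms follow an active programme meant to improve balance, so both may improve. Participants admitted on a low FGA or a high FES-I will also tend to move back towards the average when measured again. A significant change within the HOLOBalance arm therefore says little about HOLOBalance against OTAGO.

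What is at stake is the study's second aim, to support the planning of a future trial: whether to run it, and at what size.

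**Working it through.** **Inputs from the article.** 60 per arm, 1:1, and 11 instruments measured before and after. The total of 120 is 2 × 60; it has no stated alpha, power, effect or SD, so there is no derivation to reproduce.

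**Assumptions not in the article.** Two-sided alpha 0.05; 80% power for a future trial; all 11 instruments tested, one score each; inter-scale correlation 0 to 0.7; the same standardised effect on every scale; no drop-out.

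**1. False favourable signal.** With no true effect, each scale has a 0.025 chance of a significant result favouring HOLOBalance. If the scales are independent, P(at least one) = 1 − 0.975^11 = 0.243. Simulation with equal correlation between scales (200,000 runs) gives:

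| Inter-scale correlation | P(at least one favourable p<0.05) |
|---|---|
| 0 | 24% |
| 0.3 | 19% |
| 0.5 | 15% |
| 0.7 | 11% |

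**2. Missed effect.** On final scores, the SE of a standardised difference is √(2/60) = 0.183, so the 95% confidence interval is the estimate ± 1.96 × 0.183 = ± 0.36 SD. At a true effect of 0.3 SD, power is Φ(0.3/0.183 − 1.96) = Φ(−0.32) ≈ 38%. At 0.2 and 0.5 SD it is 19% and 78%.

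Using the baseline helps but does not cure this. With an assumed baseline to follow-up correlation of 0.6:
- Change scores, which the group-by-time term in a two-occasion repeated measures ANOVA amounts to: SE = √(4 × 0.4/60) = 0.163, power Φ(0.3/0.163 − 1.96) ≈ 45%.
- Baseline-adjusted analysis: SE = √(2 × (1 − 0.36)/60) = 0.146, power Φ(0.3/0.146 − 1.96) ≈ 54%.

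**3. Within-group tests.** Suppose both arms improve equally, by 0.3 SD of the change score. Each arm is significant with probability Φ(0.3 × √60 − 1.96) = Φ(0.36) ≈ 0.64. HOLOBalance significant and control not: 0.642 × (1 − 0.642) = 0.23. At an equal improvement of 0.4 or 0.5 SD this falls to 11% and 3%.

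**4. Size of the next trial, under a rule the article does not state.** Suppose the largest of the 11 observed effects were used. The number per arm is 2 × (1.96 + 0.84)²/d² ≈ 15.7/d². Ranges run from correlation 0.7 to 0.

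| True effect | Median largest observed | Planned per arm | Needed per arm | Shortfall |
|---|---|---|---|---|
| 0.2 | 0.36 to 0.48 | 123 to 68 | 393 | 3.2 to 5.8 times |
| 0.3 | 0.46 to 0.58 | 75 to 47 | 175 | 2.3 to 3.7 times |
| 0.5 | 0.66 to 0.78 | 37 to 26 | 63 | 1.7 to 2.4 times |

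**5. Size of the next trial from the pilot SD.** With 118 degrees of freedom the 95% limits for the true SD are 0.89 to 1.15 times the estimate. Required N scales with the SD squared, so the uncertainty in N is a factor of 0.79 to 1.31. Planning on the upper 80% limit multiplies the SD by 1.06 and N by 1.06² ≈ 1.12.

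**The case against.** The strongest reply is that the article commits to very little. The sentence in Trial design pairs the trends with a comparison of acceptability and speaks only of exploring. The primary outcomes are acceptability, safety and feasibility. Lack of power is disclosed, and no significance threshold is set; p<0.05 above is an assumed reading of a trend. This stands to the extent that trends cannot be called the sole or deciding basis for a future trial.

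A reader might infer that the next trial will be badly undersized because it will be sized on the best-looking scale. The documents do not support that. They say only that the study will supply data for a sample size estimate, and an SD, a correlation or a drop-out rate would fit those words equally well. Step 4 shows what one possible choice would cost, and that the cost depends strongly on the true effect.

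A reader might also object that the selected outcomes are not named. That is not a defect here: the article says an analysis plan exists, and that plan, which is not shown, may name them.

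Regression to the mean affects change within each arm, not the randomised comparison. It concerns only those who enter on FGA or FES-I, and the article gives no figures from which to size it. Nor does the article say that within-group change will be taken as evidence of effectiveness.

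Finally, testing all 11 instruments with an equal effect on each is a simplification. Fewer tested scales would lower the figures in step 1; scoring the six CANTAB tasks separately would raise them. Low power per scale does not depend on the number of scales, and naming the outcomes in an analysis plan would not remove it.

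**Conclusion.** The point holds as a weakness in the stated basis for progression. The article links whether a further trial is warranted to effectiveness trends that it says it lacks the power to analyse formally, and it plans within-group tests that cannot separate HOLOBalance from OTAGO.

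On the assumptions above, a null intervention shows at least one favourable p<0.05 in about 11% to 24% of studies. A true 0.3 SD effect is detected on a given scale about 38% of the time on final scores, and about 54% with baseline adjustment at correlation 0.6. Equal improvement of 0.3 SD in both arms leaves HOLOBalance alone significant about 23% of the time. The plan invites these errors and does not make them certain. Undersizing of the next trial is conditional on a selected observed effect being used, which the article does not say. The point deserves a change because the remedy is cheap and bears directly on the study's second aim.

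**What to change.** Amend the Trial design section and the section on data management and statistical analysis to state four things:

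1. Progression to a future trial rests on the primary outcomes (compliance, drop-out, safety and feasibility). Effectiveness results are descriptive support.
2. Effectiveness is reported as baseline-adjusted between-group differences with 95% confidence intervals, for every scale measured before and after.
3. Within-group tests are not used as evidence of effectiveness; within-arm change may still be described.
4. The future trial is sized from the pilot's SD, allowing for its uncertainty (for example its upper 80% limit), and from a target difference set outside the pilot.

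The cost is wording only, with no new data and no extra participants. The downsides are fewer nominally positive statements and a somewhat larger planned future trial: about 12% more participants if the upper 80% limit is used with 118 degrees of freedom.

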**Figure 1 F1:**
[figure not shown]
CONSORT diagram to demonstrate participant flow through the HOLOBalance study. CONSORT, Consolidated Standards of Reporting Trials.

### Participants

One hundred and twenty independently living, community-dwelling older adults aged 65–80 who are at risk of falls will be recruited across three sites (London (UK), Freiberg (Germany), Athens (Greece)). Older adults who meet the following inclusion criteria for entry will be eligible to be enrolled.

### Inclusion criteria

Independent community-dwelling participants able to walk 500 m independently or with a stick.No significant visual impairment.Able to understand and to consent to the research.A score of >22 on the Montreal Cognitive Assessment (MoCA), that is, adults with no or mild cognitive impairment.At risk of falls (ie, Functional Gait Assessment, FGA less than 22/30), and / or have significant fear of falling (Falls Efficacy Scale International (FESI) short form >10) and /or have experienced a fall/s in the last 12 months.Willing to participate and to comply with the proposed training and testing regimen.Available space of 1×2 m at home and sufficient home broadband to allow the system to operate as designed.

### Exclusion criteria

Orthostatic hypotension or uncontrolled hypertension.Have depression that is, a score of >10 at the Geriatric Depression Scale.Have cognitive impairment as indicated by the MoCA score(score <22).Other neurological problem (eg, stroke, Parkinson’s disease, peripheral neuropathy).Acute musculoskeletal injury that prevents participation in a structured exercise programme (eg, lower limb fracture).No internet connection at home.Has participated in a clinical drug trial in the past 6 months.Currently receiving falls and/or cognitive rehabilitation.Has an implanted medical device or cardiac pacemaker.

### Recruitment

Community-dwelling older adults will be recruited via adverts placed in the community, on social media and by referrals made by recruiting clinics. Potential participants will undergo a telephone screening session with a researcher to determine their eligibility, with eligible participants booked in for baseline testing with the blinded outcome assessor. Participants will provide written informed consent on arrival at their baseline outcome assessment session.

